Information nudges for influenza vaccination: Evidence from a large-scale cluster-randomized controlled trial

*Research plan / study protocol*

[name], [name], [name],

[name], [name], [name]

*1. Introduction*

Vaccination is often considered to be one of the most effective and successful means of preventive medicine (WHO, 2013). However, increasing levels of vaccine hesitancy pose a serious threat to the success of various vaccination programs (MacDonald, 2015 and Schmid et al., 2017). A prominent example of vaccination hesitancy is vaccination against seasonal influenza. Even though influenza is estimated to lead to 3 to 5 million cases of severe illness and 250.000 to 500.000 deaths every year (WHO, 2014), low influenza vaccine coverage within specific risk groups remains a challenge throughout the globe (WHO, 2015). In many countries, vaccinating against seasonal influenza is recommenced for all individuals aged 65 and above and vaccines are offered free of charge to all individuals in this age group. Despite the recommendation and low individual cost of vaccinating, the rates of influence vaccinations constantly remain below the socially optimal levels in the target populations.

Low rates of vaccination coverage put both the vaccine refusers and public health at risk. The herd immunity threshold required to indirectly protect unvaccinated individuals due to reduced pathogen spreading in the population is in many cases not reached (Fine et al., 2011). However, with increasing vaccination rates, herd immunity may effectively prevent the infection of people who are not able to get vaccinated themselves because, for instance, they are too young or immunocompromised. Considering the positive effect of one’s own vaccination on others, vaccination is also an act of pro-sociality (Betsch et al., 2013 and Betsch et al., 2017)

The aim of proposed research is to test the effectiveness of communicating the concept of herd immunity on actual influenza vaccine coverage in a naturally-occurring setting using a randomized controlled trial.

*2. Conceptual framework*

Using behavioural insights to increase individual vaccine uptake has received increasing attention and is considered to be a promising tool to increase vaccination uptake (Betsch et al. 2015). Here, we propose to test the effectiveness of a novel behavioural intervention building on the communication of herd immunity. Previous laboratory and online experiments have shown that communicating the concept of herd immunity increases individuals’ (hypothetical) intention to get vaccinated (Betsch et al., 2013, Betsch et al., 2017 and Böhm et al., 2018). The positive effect of communicating the concept of herd immunity is particularly pronounced when (*i*) the vaccination uptake rate is low (vs. high), (*ii*) the individual vaccination costs are low (vs. high), (*iii*) the social benefit (vs. the individual benefit) of herd immunity is emphasized, (*iv*) the beneficiaries of herd immunity are not able (vs. not willing) to get vaccinated themselves, and (*v*) the communication is based on an interactive simulation (vs. text-based explanation). However, despite the accumulating evidence regarding the effectiveness and boundary conditions of communicating herd immunity on vaccination attitudes, previous research has exclusively relied on hypothetical vaccination decisions under highly controlled conditions.

The aim of the present research is to test the effectiveness of communicating the concept of herd immunity on actual influenza vaccine coverage in a naturally-occurring setting using a randomized controlled trial. In addition to a control condition (no information about vaccination campaign against seasonal influenza), we propose two treatments that employ different strategies to inform citizens about the benefits of influenza vaccines. The treatment containing information about the herd immunity is based on previous studies of hypothetical vaccination decisions.

We are going to conduct a randomized controlled trial among older adult population in Finland. The National Institute for Health and Welfare (PIs [name] and [name]) will administer and conduct the studies. Participants will be Finnish individuals across several municipalities for whom influenza vaccination is recommended (aged 65 years and above).

*3. Experimental design*

We run a large-scale natural field experiment to understand the behavioural processes that guide decisions to vaccinate and test alternative strategies to communicate the concept of herd immunity. The experiment varies the text of postal letters send to individuals eligible for free influenza vaccines. The experiment is run in collaboration with the municipal health authorities. The municipalities that have confirmed their participation in the study are: Espoo, Maalahti, Korsnäs, Närpiö, Kaskinen ja Kristiinankaupunki.

We implement the randomized study in municipalities with varying historical vaccination uptake rates (historical and current vaccination coverage based on the Finnish vaccination register). Implementation in different municipalities with different current vaccination rates will give further information about the generalizability of the findings in different cultural and socio-economic environments and may enable us to test the average indirect effect of the treatments (Spillover effect, see section 4.5)

We identify using the Population Register all individuals who are born in year 1953 or before and resided in the participating municipality on July 01, 2018. We will obtain the postal addresses of these individuals using the Population Register and randomly assign individuals to treatment conditions that differ in the wording of the information material. Note that we will send the same letter separately to both individuals residing in the same address to avoid the situation that same persons living in the same household receive letters with different wordings. Importantly, the extract from the Population Register will also include an individual identifier (social security number) that can be used to match the received type of letter (treatment) with the actual vaccination decision recorded in the Care Register for Health Care to objectively evaluate the impact of received information on vaccination coverage. The matching of postal addresses and vaccination data will be conducted using pseudonymized identifiers. The pseudonymization of individual identifiers will be performed separately for both datasets by professional data management and data security staff of the National Institute for Health and Welfare. Consequently, the researchers conducting the data analysis will be able to access only pseudonymous data without a possibility to directly identify individuals from the data set. The data will be stored according to the data protection legislation and regulations of the National Institute for Health and Welfare during the research project.

We randomly assign individuals to treatment conditions that differ in the wording of the letters (attached). The authority’s standard letter serves as the baseline condition (T1). This letter is extended by communicating the concept of *herd immunity* and appealing to *pro-social preferences* by highlighting the fact that vaccinations may effectively prevent infections among people who are not able to vaccinate themselves (especially babies) (T2). To summarize, our study includes a control treatment (T0, no letter) and two treatment arms with the following contents: T1 – Standard letter, T2 – Herd immunity letter.

*4. Analysis Plan*

*4.1 Unit of Analysis*

Our primary outcome variable is individual level vaccination decision. In addition, we estimate average treatment effects by municipality and test whether different treatment arms have uniform effects across municipalities that differ in their baseline vaccination coverage.

*4.2 Average treatment effects*

We run the following linear probability model to estimate the average treatments effects:

$Y_{i}=\alpha+\beta_{1}Mailing+\beta_{2}Herd+\varepsilon_{i}$,

where $Y_{i}$ indicates whether individual *i* has received an influenza vaccine by the end of influenza season 2018 - 2019. Variable *Mailing* indicates whether individual *i* is in a mailing group or in the control group receiving no mailings. Variable *Herd* is a treatment dummies indicating whether individual *i* belongs to a treatment arm with herd immunity information. We cluster standard errors at the household level to account for correlation at the household level.

In addition to our primary interest on the overall effectiveness of different treatment arms, we investigate the effect of mailings by municipalities that vary in their baseline vaccination rates and estimate the following equation using linear probability model:

$Y_{i,t}=\alpha+\beta_{1}{Mailing}_{t}+\beta_{2}{Baseline}_{t-1}+\beta_{3}Mailing*{Baseline}_{t-1}+\varepsilon_{i,t}$,

where variable *Baseline* denotes the vaccination coverage by municipality in the previous year (2017). Thus, $\beta_{3}$ shows the differential average treatments effect of mailing by municipality.

We run all estimations primarily using linear probability models to improve comparability between estimations as estimating equations with interaction terms and computing correct interaction effects in non-linear models may require tedious computing (Ai and Norton, 2003.

*4.3 Statistical power*

We present in the following some standard power estimates to assess the minimum detectable effect size. Figure 1 shows the minimum detectable (absolute) effect size between two treatments as a function of sample size with test power .80 and .90. Power calculations are based on treatment comparisons using linear probability model. Here we assume that alpha = 0.05 (two-sided). Figure 2 shows the minimum total sample size needed to detect a standardized effect size varying from 0.05 to 0.25 (assuming test power .80 and alpha 0.05). Note that the power calculations do not account for potential corrections for multiple hypotheses testing or clustering of standard errors to account for potential correlation of standard errors.

[figure not shown]

Figure 1. Minimum detectable effect size as a function of sample size and statistical power.

[figure not shown]

Figure 2. Minimum total sample size needed to detect a standardized effect size varying from 0.05 to 0.25 (assuming test power .80 and alpha 0.05).

*4.4 Attrition*

We do not expect significant attrition. The expected main sources of attrition are migration from the municipality and mortality. Migration from the target municipality to abroad during study period is expected to be less than 5 percent. We expect that attrition is not correlated with the treatment status.

*4.5 Spillover effects*

Our RCT is based on household-level randomization. The institutional context, the large coverage of target groups and relatively short study period (from the reception of letter until the end influenza season) are likely to substantially limit potential spillover effects between the treatment arms and control group. We design the implementation of various treatment arms such that two (or more) individuals over 65-years of age living in the same household will be assigned to same treatment arm. This practice eliminates potential spillover effects between individuals living in the same household.

The main concern related to potential spillover effects pertains to the treatment comparison between non-treated individuals and treated individuals (in any treatment arm). It is important to note that our main outcome is vaccination coverage which is unlikely to cause substantial externalities and affect the *vaccination coverage* of individuals who do not receive any letter informing the recipient about the upcoming influenza season. Likewise, there is no room for general equilibrium effects where (expected) increase in vaccination coverage in treatment groups would affect the supply of vaccines. The most notable potential channels of spillover effects between control and treatments groups operate through social interaction between the non-treated and treated individuals. For example, individuals who receive letters may share their information about the herd effect with non-recipients. It is difficult to ex ante assess if this kind of spillovers may lead us to underestimate the true effect of the mailings.

Despite the limited size of potential spillover effects, our experimental design where we assign individuals into treatments in several municipalities may enable us to measure the effect of treatments also on the non-treated individuals. There are three distinct types of individuals defined by individual treatment status and place of residence: (i) Treated individuals in the treated municipalities receiving mailing, (ii) non-treated individuals in treated municipalities who do not receive mailings, but may be indirectly affected by the treatment, (iii) non-treated individuals in non-treated municipalities who are not affected (assuming that the potential spillover effects occur only within treated municipalities). Thus, the presence of these three types of individuals enables us to estimate the Average Treatment Effect (ATE) and the average Indirect Treatment Effect (ITE).

$$ATE=E\left( Y_{1}-Y_{0} \right|T=1, M=1)=E\left( Y | T=1,M=1 \right)-E(Y|T=0,M=1)$$

$ITE=E(Y_{1}-Y_{0}\left| T=0,M=1 \right)=E\left( Y | T=0,M=1 \right)-E(Y|T=0,M=0)$,

where Y is the outcome (Decision to vaccinate), T is individual treatment status and M is an identifier for the municipalities sending mailings to their citizens. However, note that we estimate the ITE accurately if spillover effects occur only within the treated municipalities.

*5. Data Management*

We will follow the general Finnish guidelines on research ethics for research data management (for a more detailed description of data management see the separate data management plan). In addition, we will follow the data availability policy applied by targeted journals.

The linked data sets will be made available to all interested researchers during the whole research period given that the researchers have acquired appropriate data permissions according to Finnish data protection legislation. The data permission procedures will be handled by the professional staff in charge of the data management and security at the Finnish National Institute for Health and Welfare. Since the register databases include sensitive individual-level information, only pseudonymized merged dataset without direct identifiers will be made available to interested researchers.

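### The primary model leaves out municipality, and no allocation ratio is stated: intercepts would add a little precision and guard the mailing effect against unequal arm shares

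*Protocol*

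**What the plan says.** Section 3 (Experimental design) lists the participating municipalities: "Espoo, Maalahti, Korsnäs, Närpiö, Kaskinen ja Kristiinankaupunki". It describes the setting in these terms: "We implement the randomized study in municipalities with varying historical vaccination uptake rates". Eligible persons are found in the Population Register by year of birth and by municipality of residence on a fixed date, so municipality is known for everyone before assignment.

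Assignment is described as random in Section 3. Section 4.5 gives the unit: "Our RCT is based on household-level randomization". Neither section gives an allocation ratio or arm shares by municipality, or says whether assignment is stratified.

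Section 4.2 introduces the primary analysis: "We run the following linear probability model to estimate the average treatments effects". The model is Y = α + β1·Mailing + β2·Herd + ε. On inference it adds: "We cluster standard errors at the household level to account for correlation at the household level". Municipality appears only in the further analyses: effects by municipality (Sections 4.1 and 4.2), and a second equation with Mailing, the municipality's 2017 coverage (Baseline) and their product. Section 4.5 refers to "our experimental design where we assign individuals into treatments in several municipalities" and defines the average treatment effect within mailing municipalities only.

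**The concern.** The protocol treats differing municipal uptake as a feature of the design and as a dimension of the analysis, but the primary equation does not use it. With one intercept, β1 compares pooled arm means. That comparison is free of municipal differences in expectation only if the chance of receiving a letter is the same in every municipality, and the protocol does not state this condition.

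Two things are at stake. The certain one is small: a known predictor of the outcome is left in the error term. The conditional one could be larger: if the no-letter share differed between municipalities for any reason, the control group and the letter groups would have a different municipal mix, and part of the uptake gap would be read as a letter effect. Household-clustered standard errors would not reveal this, because it would be a shift in the estimate and not extra noise.

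**Working it through.** The readable protocol gives no sample size, uptake rate or arm share, so there is no stated figure to reproduce. Every input below is an assumption except where a section is named.

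**1. One assignment probability everywhere.** The expected share of each municipality is then the same in all arms, and the expected bias is 0. A simulation of simple household randomisation used a letter probability of 2/3, one or two persons per household, 5,000 to 40,000 persons, uptake gaps of 5 and 20 points, and a large-municipality share of 50% or 90%.
- Mean shift: within 0.011 points of zero in every setting.
- SD of the shift from chance imbalance: 0.02 to 0.39 points.
- Standard error of the effect (independent data, 50% rate): 1.50 points at 5,000 persons, 0.53 at 40,000.

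This is ordinary sampling variation, already contained in the standard error.

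**2. Precision gain from intercepts.** Share of outcome variance explained ≈ (between-municipality SD)² / [p(1−p)], with p = 0.5:
- SD 5 points: 0.05²/0.25 = 1.0%
- SD 8 points: 0.08²/0.25 = 2.6%

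**3. Unequal arm shares.** For two strata, bias in β1 = uptake gap × difference in stratum share between the letter group and the controls. Assume the large municipality holds 80% of persons, the control share is 1/3 there and 1/2 elsewhere, and the gap is 15 points.
- Small-municipality share of controls: 0.2×0.5 / (0.8/3 + 0.2×0.5) = 0.100/0.367 = 27.3%
- Small-municipality share of the letter group: 0.2×0.5 / (0.8×2/3 + 0.2×0.5) = 0.100/0.633 = 15.8%
- Bias: (0.273 − 0.158) × 15 = 1.7 points. It is upward if the large municipality has the higher uptake, downward otherwise.

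Range over gaps of 5 to 20 points and large-municipality shares of 50% to 90%:

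| Letter probability, large vs other | Absolute bias in β1 (points) |
|---|---|
| 2/3 vs 2/3 | 0 |
| 2/3 vs 0.60 | 0.13 to 1.44 |
| 2/3 vs 0.50 | 0.33 to 3.43 |
| 0.80 vs 0.50 | 0.76 to 6.59 |

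For scale, the smallest standardised effect in Section 4.3 is 0.05, which is 0.05×0.5 = 2.5 points at a 50% rate.

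**4. Which coefficient.** Mailing is 1 for both letters, so β2 contrasts the herd letter with the standard letter among persons who were mailed. If the T1:T2 split is the same everywhere, both letter groups have the same municipal mix and β2 has no bias, even in step 3.

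**5. What intercepts do.** With municipality intercepts and a constant effect, the bias in step 3 is 0 whatever the shares. If effects differ by municipality, the adjusted letter versus no-letter contrast weights each municipality by (its share of persons) × p(1−p), where p is its letter probability. Under step 3 the weights are 0.8×0.222 = 0.178 and 0.2×0.25 = 0.050, so the small municipalities count for 0.050/0.228 = 22% against 20% of persons. With equal shares the weights match the population.

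**6. Second equation.** Baseline has one value per municipality, so municipality intercepts absorb its main effect. The Mailing-by-Baseline product varies within municipality and stays estimable.

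**The case against.** The strongest reply is that nothing in the protocol suggests unequal arm shares. Section 3 describes one register extract followed by random assignment, and a common probability is the natural reading. Under that reading the primary model is valid as written. The bias in step 3 comes wholly from assumed shares, and covariate adjustment is often left to a SAP, which is not at hand. Effects by municipality are planned anyway; they are immune to this bias and would expose a discrepancy. Section 4.5 also keeps non-mailing municipalities out of the average treatment effect. All of this stands, and it limits the point to a modest one.

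What it does not remove is that Section 4.2 writes the primary equation out in full, so the omission of municipality is a stated choice.

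A reader might infer more than the protocol supports:
- That assignment is not stratified. The protocol is silent on this. Nor is stratification the deciding fact: unstratified assignment at one probability is unbiased, while stratified assignment with unequal shares would be biased without intercepts.
- That chance imbalance in the small municipalities biases the estimate. Step 1 shows that it does not.
- That the municipalities were picked because their uptake differs. Section 3 says only that they confirmed participation and that uptake varies.

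**Conclusion.** The point holds as an improvement to the primary model and a missing statement about allocation. It is not a demonstrated bias. What can be said without knowing the arm shares is that municipality is a known predictor left out of the primary equation, at a cost of about 1-3% of variance if the between-municipality SD is 5-8 points and uptake is near 50%. Whether there is any bias depends on the arm shares, which the protocol does not give: it is zero at a common ratio, and 1.7 points in β1 under the assumptions of step 3. That would be of the same order as the smallest effect considered in Section 4.3. It would be tempting to extend this to the herd-immunity contrast β2, but that needs the T1:T2 split itself to vary by municipality, and nothing in the protocol indicates this.

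**What to change.** - **Primary equation, Section 4.2:** replace the common intercept by municipality intercepts (five dummies for six municipalities) and keep the household-clustered standard errors.
- **Section 3:** state the allocation ratio for T0, T1 and T2, and that households are assigned at this one ratio within every municipality. If shares differ by design, give them.
- **Second equation, Section 4.2:** if intercepts are used here too, drop the Baseline main effect and keep Mailing and the Mailing-by-Baseline interaction.
- **Interpretation:** state that, if effects differ between municipalities and shares are unequal, the adjusted coefficient is a variance-weighted average of the municipal effects.

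The cost is five parameters and a few sentences, with no new data. The only drawback is the weighting just described, which disappears at a common ratio.

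### Section 4.1 promises a test of arm-specific effects by baseline coverage, but the only heterogeneity equation in 4.2 pools both letters into one Mailing dummy

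*Protocol*

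**What the plan says.** Protocol section 3 defines three arms: "our study includes a control treatment (T0, no letter) and two treatment arms with the following contents: T1 – Standard letter, T2 – Herd immunity letter".

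Section 4.1 promises, besides the individual-level primary outcome, average treatment effects by municipality and a test to "test whether different treatment arms have uniform effects across municipalities that differ in their baseline vaccination coverage".

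Section 4.2 then writes two linear probability models.

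- The first regresses vaccination on Mailing and Herd. Mailing "indicates whether individual *i* is in a mailing group or in the control group receiving no mailings". Herd is a dummy "indicating whether individual *i* belongs to a treatment arm with herd immunity information". The Mailing coefficient is thus T1 minus T0, and the Herd coefficient is T2 minus T1.
- The second is introduced with "we investigate the effect of mailings by municipalities that vary in their baseline vaccination rates". It contains Mailing, Baseline (municipal coverage in the previous year, 2017) and Mailing × Baseline. It has no Herd term and no Herd × Baseline term. The protocol says that its interaction coefficient, β3, "shows the differential average treatments effect of mailing by municipality".

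As background, section 2 reports from laboratory and online studies of hypothetical decisions: "The positive effect of communicating the concept of herd immunity is particularly pronounced when" certain conditions hold. The first of the five conditions listed is low vaccination uptake.

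**The concern.** Section 4.1 speaks of different arms, while the section 4.2 equation speaks of any letter against none. No other section supplies an arm-specific interaction. This is not a detail left for a later document, because the protocol writes the equation out and says how its coefficient is to be read.

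The pooled β3 answers whether the effect of receiving a letter varies with municipal coverage. It does not answer whether the added effect of herd-immunity information varies with coverage, nor whether both arms have uniform effects. Results from the written model would leave the question in 4.1 open, and an arm-specific interaction added after the data are seen would be post hoc.

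**Working it through.** The protocol prints no figure for this analysis, so there is nothing to reproduce. The check concerns what the written model identifies.

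**Inputs from the protocol.** Three arms (section 3); Mailing = 1 for T1 and T2, and Herd = 1 for T2 only (section 4.2); six confirmed municipalities (section 3); two-sided alpha 0.05 (section 4.3).

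**Assumptions, not in the protocol.** The allocation ratio, municipality sizes and baseline coverages are not stated. I take the same T1:T2 ratio in every municipality. For the numerical check I use six baselines between 30% and 50%, with one municipality holding 80% of the sample.

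**1. What β3 measures.** Let g1 and g2 be the slopes on Baseline of the T1 and T2 effects against T0, and q the share of mailed people in T2. Then

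β3 = (1 − q)·g1 + q·g2.

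With s = g1 and h = g2 − g1, this is s + q·h.

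**2. Numerical check.** A noise-free weighted least-squares fit was made of the written model and of the model with Herd and Herd × Baseline added.

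| True g1, g2 | T1:T2 | Written model, β3 | Added model, Mailing × Baseline | Added model, Herd × Baseline |
|---|---|---|---|---|
| 0, −0.4 | 1:1 | −0.200 | 0.000 | −0.400 |
| −0.2, −0.2 | 1:1 | −0.200 | −0.200 | 0.000 |
| −0.4, 0 | 1:1 | −0.200 | −0.400 | +0.400 |
| +0.2, −0.2 | 1:1 | 0.000 | +0.200 | −0.400 |
| 0, −0.4 | 6:4 | −0.160 | 0.000 | −0.400 |

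The first three rows are different answers to the question in 4.1, yet the written model returns the same coefficient for each. The fourth row is real heterogeneity that it does not show. The fifth shows that β3 also depends on the allocation ratio: 0.4 × (−0.4) = −0.160. The added model has full rank (6 of 6 columns) and recovers both slopes.

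**3. Power if the gradient is confined to T2.** Take equal arms of n, with equal residual variance and the same spread of Baseline in each arm. The variance factors are:

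- pooled letters against control: 1/n + 1/(2n) = 1.5/n;
- T2 against T1: 1/n + 1/n = 2/n.

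The pooled slope is half the T2 slope, so the ratio of non-centralities is (0.5/√1.5)/(1/√2) = 0.577. If the direct Herd × Baseline test has 80% power (non-centrality 2.80), the pooled test has Φ(2.80 × 0.577 − 1.96) = Φ(−0.34) ≈ 0.37.

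**4. Power if the gradient is common to both letters.** Here pooling helps. If pooled β3 has 80% power, the Mailing × Baseline term of the added model (T1 against T0, factor 2/n) has non-centrality 2.80 × √(1.5/2) = 2.43 and power Φ(2.43 − 1.96) ≈ 0.68. The joint two-degree-of-freedom test of both interactions, with non-centrality 2.80² ≈ 7.85, has power of about 0.71.

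**The case against.** Several points on the other side are sound.

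- **The analysis is secondary.** Section 4.2 places it after the primary interest in the overall effectiveness of the arms. The stated aim, the effect of communicating herd immunity, is addressed by the Herd coefficient of the first equation. This stands and limits the severity.
- **The pooled equation does what 4.2 says.** It is worded as a model of mailings, and for a gradient common to both letters it is the more powerful choice (80% against about 68%). This stands. It argues against deleting the pooled model, but it does not supply the test named in 4.1.
- **Section 4.1 also mentions effects by municipality.** Fitting the first equation within each municipality would give herd-specific effects. That is true, but no such model and no test across municipalities is written.

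A reader might also infer more than the document supports:

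- *That the trial's founding hypothesis cannot be tested.* Section 2 cites moderation by uptake as earlier evidence, one of five conditions, and never labels it a hypothesis of this trial. Section 3 gives other reasons for using municipalities with varying uptake: generalizability and possibly the spillover effect.
- *That the arm-specific interaction cannot be estimated at all.* This is true only of the written equation. Section 3 provides for linking each person's letter type to the vaccination record, and the added model has full rank.
- *That β3 would be reported as a herd effect.* The protocol consistently calls it an effect of mailing.
- *That leaving Baseline uncentred is an error.* Centring changes neither β3 nor its test, and the protocol interprets no other coefficient of that equation.

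**Conclusion.** The mismatch between sections 4.1 and 4.2 is real and nothing elsewhere in the protocol resolves it. As written, β3 is an allocation-weighted average of two slopes and cannot deliver the test of uniform effects by arm. That conclusion follows from the coding of Mailing and does not depend on the assumed baselines or municipality sizes.

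The size of the power loss is conditional. The fall from 80% to about 37% applies only with equal arms and a gradient confined to the herd letter; for a common gradient the comparison runs the other way. The point is worth correcting before analysis, but it concerns a secondary analysis and leaves the main estimate of the herd effect untouched.

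**What to change.** Keep the pooled Mailing × Baseline model as the analysis of any mailing, and add beside it:

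Y = a + b1·Mailing + b2·Herd + b3·Baseline + b4·Mailing × Baseline + b5·Herd × Baseline + e.

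Name b5 as the test of whether the herd-immunity increment varies with baseline coverage, and the joint test b4 = b5 = 0 as the test of uniform effects of both arms. Centring Baseline is optional.

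Alternatively, reword section 4.1 so that it promises only heterogeneity of the effect of any mailing.

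Under either choice, state that with the six confirmed municipalities Baseline takes at most six distinct values, so the interaction tests have limited precision.

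The cost is one equation and two or three sentences, or one reworded sentence plus the note on precision. No new data are needed.
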